## 1. Scope

This Statistical Analysis Plan (SAP) describes the outcomes and analyses for the long term follow-up of the Australasian Collaborative Trial of Repeat Doses of Steroids (ACTORDS). In this plan the mothers who participated in ACTORDS are referred to as the F0 generation and their children the F1 generation. This SAP concerns the twenty-year follow-up of children (F1 generation) of the participants of ACTORDS. This follow-up study was conducted as part of the AnteNatal Corticosteroids Health Outcomes Review (ANCHOR) Study.

## 2. Study information

### Aim

To determine if repeat antenatal corticosteroids, given to women at risk of preterm birth, have long term impacts on the health of offspring (F1).

### Study hypothesis

Repeat antenatal corticosteroids reduce neonatal mortality and morbidity without long-term adverse impacts on health and social outcomes in offspring (F1).

## 3. Background: The Australasian Collaborative Trial of Repeat Doses of Steroids (ACTORDS)

### ACTORDS RCT

In this multicentre centre, two-arm, parallel, randomised double blind placebo-controlled trial, women who remained at risk of preterm birth at less than 32 weeks' gestation, 7 or more days after receiving a first course of prenatal corticosteroids, were randomly assigned to receive a repeat intramuscular dose of either betamethasone or saline placebo. This could be repeated every week the woman remained undelivered, at less than 32 weeks' gestation, if still considered to be at risk of preterm birth in the next 7 days. Primary outcomes were occurrence and severity of neonatal respiratory distress syndrome, severity of any lung disease present, use and duration of oxygen and mechanical ventilation, and weight, length, and head circumference at birth and hospital discharge.

The RCT found that fewer babies exposed to repeat corticosteroids had respiratory distress syndrome and fewer had severe lung disease than those in the placebo group. In keeping with these benefits, babies exposed to repeat corticosteroids needed less oxygen therapy, and shorter duration of mechanical ventilation. Mean weight, length, and head circumference at birth and hospital discharge did not differ between treatment groups. Z-scores for weight and head circumference at birth were lower in the babies who received repeat corticosteroids although at the time of hospital discharge Z-scores did not differ between treatment groups.

### 2-year follow-up

The primary outcome of the 2-year follow-up study was survival free of major neurosensory disability and body size of the children at 2 years of corrected age.

Of the 1085 children who were alive at 2 years of age, 1047 (96.5%) were seen for assessment (521 exposed to repeat-corticosteroid treatment and 526 exposed to placebo). The rate of survival free of

major disability was similar in the repeat corticosteroid and placebo groups (84.4% and 81.0%, respectively; adjusted relative risk, 1.04, 95% confidence interval, 0.98 to 1.10; adjusted  $P = 0.20$ ). There were no significant differences between the groups in body size, blood pressure, use of health services, respiratory morbidity, or child behaviour scores, although children exposed to repeat doses of corticosteroids were more likely than those exposed to placebo to warrant assessment for attention problems ( $P = 0.04$ ).

### 6–8-year follow-up

The primary outcome of the mid-childhood follow-up study was survival free of neurosensory disability.

Of the 1059 eligible long-term survivors, 963 (91%) were included in the primary outcome; 479 (91%) in the repeat corticosteroid group and 484 (91%) in the placebo group. The rate of survival free of neurosensory disability was similar in both groups (78.3% repeat versus 77.3% placebo; risk ratio 1.00, 95% confidence interval, 0.94–1.08). Neurodevelopment, including cognitive function, and behaviour, body size, blood pressure, spirometry, and health-related quality of life, were similar in both groups, as was the use of health services.

A secondary analysis was also undertaken to determine the influence of fetal growth restriction (FGR) on the effects of repeated doses of antenatal betamethasone on neurocognitive function in mid-childhood. The FGR rate was 139 of 493 children (28.2%) in the repeat betamethasone treatment group and 122 of 495 (24.6%) in the placebo group. The rates of the primary outcomes, survival free of any disability and death or moderate to severe disability, were similar between treatment groups in both the FGR and non-FGR subgroups, with no evidence that FGR influenced treatment effect.

### In-depth 6–8-year follow-up of the New Zealand ACTORDS cohort

In the New Zealand ACTORDS cohort, an extended follow-up was undertaken to investigate the long-term effects of repeat antenatal betamethasone treatment on risk factors for cardiovascular and metabolic disease and bone health. The children had to be living in New Zealand to be eligible, so this cohort included some children randomised in Australia but living in New Zealand, and excluded some randomised in New Zealand but living elsewhere.

Of 320 eligible childhood survivors for the study of cardiometabolic risk factors, 258 were assessed (81%; 123 repeat betamethasone group; 135 placebo [single course] group). Children exposed to repeat antenatal betamethasone and those exposed to placebo had similar whole-body and regional fat and lean mass; insulin sensitivity, acute insulin secretion and fasting glucose and insulin concentrations; ambulatory blood pressure and heart rate, including nocturnal; and estimated glomerular filtration rate.

Of 212 childhood survivors eligible for whole-body dual-energy radiograph absorptiometry to assess bone mass, 185 were studied (87%; 91 repeat betamethasone group; 94 placebo [single course] group). Children exposed to repeat antenatal betamethasone and those exposed to placebo had similar whole-body and spinal bone mineral content and bone area, and risk of fractures.

## 4. Methods for the ANCHOR Study: follow-up of ACTORDS F1

### Study design

This study consists of long term follow-up of ACTORDS at 20 years comparing outcomes in offspring (F1) exposed to repeat prenatal betamethasone to those exposed to placebo (single course of corticosteroids).

Follow-up consisted of a questionnaire based on the New Zealand Health Survey and consent to accessing routinely collected data from government agencies including the Ministry of Health, Testsafe, Ministry of Education, New Zealand Qualifications Authority, Accident Compensation Corporation, Ministry of Justice, Whaikaha (Ministry of Disabled People) and Statistics New Zealand.

### Inclusion Criteria

Participants in this follow-up study were eligible for inclusion if they had been born to a participant in ACTORDS who was randomised in New Zealand and written informed consent was obtained. Participation in the 2-year follow-up study or the 6–8-year follow-up study was not a requirement for participation.

### Exclusion criteria

Declined participation or unable to obtain informed consent.

## 5. Study outcomes

Outcome definitions and the hierarchical approach to different data sources are listed below and detailed in the [appendix](#). All components of the composite secondary outcomes will be reported separately as tertiary outcomes. Administrative data will be right censored at the date of the questionnaire for participants who completed the questionnaire and at the date of consent for those who did not.

### Primary Outcome

- Any asthma diagnosis

### Secondary Outcomes:

- Asthma currently on treatment
- Death (any cause after randomisation)
- Respiratory outcomes (composite) – any respiratory diagnoses other than asthma including chronic lung disease
- Neurodevelopmental disability (composite) – any of:
  - visual impairment
  - hearing impairment
  - intellectual impairment
  - cerebral palsy
  - epilepsy
  - autism spectrum disorder (including Asperger's syndrome)
  - attention deficit disorder (ADD) or attention deficit hyperactivity disorder (ADHD)
- Cardiovascular outcomes (composite) – any cardiovascular diagnosis including hypertension, cardiomyopathies, arrhythmias, heart failure but excluding congenital heart disease
- Number of cardiovascular disease risk factors (composite categorised as 0, 1 or >1 risk factors) – any of:
  - high blood pressure
  - dyslipidaemia

- diabetes mellitus
- obesity/overweight
- Diabetes outcomes (composite) – any of prediabetes, diabetes mellitus, gestational diabetes mellitus
- Mental health outcomes (composite) – any mental health diagnosis including depression, bipolar affective disorder, schizophrenia, anxiety disorders, suicide/self-harm
- Bone health outcomes: any diagnoses related to bone disease
- Bone health outcomes: number of fractures
- General health outcomes: self-reported general health (reported health fair or poor)
- General health outcomes: functional difficulties (categorised as no disability / moderate or non-severe disabilities / severe disabilities)
- General health outcomes: oral health (reported oral health fair or poor or tooth extractions)

#### **Tertiary Outcomes:**

- Educational achievement outcomes: no secondary school qualification
- Educational achievement outcomes: any disciplinary action
- Social outcomes: any convictions
- Social outcomes: unemployment
- Social outcomes: alcohol use in the past year
- Social outcomes: recreational drug use
- Social outcomes: past/current smoking (pack years)
- Social outcomes: past/current vaping
- Components of neurodevelopmental disability composite outcome:
  - visual impairment
  - hearing impairment
  - intellectual impairment
  - cerebral palsy
  - epilepsy
  - autism spectrum disorder (including Asperger's syndrome)
  - attention deficit disorder (ADD) or attention deficit hyperactivity disorder (ADHD)
- Components of cardiovascular composite outcome:
  - Hypertension
  - Cardiomyopathies
  - Arrhythmias
  - heart failure
- Components of cardiovascular disease risk factors composite outcome:
  - high blood pressure
  - dyslipidaemia
  - diabetes mellitus
  - obesity/overweight
- Components of diabetes composite outcome:
  - prediabetes/diabetes mellitus
  - gestational diabetes mellitus
- Components of mental health composite outcome
  - depression
  - bipolar affective disorder
  - anxiety disorders
  - suicide/self-harm

- schizophrenia
- Components of functional difficulties outcome
  - Difficulty seeing, even if wearing glasses
  - Difficulty hearing, even if using a hearing aid
  - Difficulty walking or climbing steps
  - Difficulty remembering or concentrating
  - Difficulty washing all over or dressing
  - Difficulty communicating
- Components of obesity/overweight outcome
  - BMI
  - height
  - weight

## 6. Outcome reporting

Outcomes may not all be reported in the same publication, instead being grouped into categories for reporting. These categories will likely include cardiometabolic and respiratory outcomes, other health outcomes and socioeconomic outcomes.

## 8. Power calculation

This study involves the follow-up of a clinical trial, and the sample size is limited to the number of participants randomised in New Zealand and able to be located. For the primary outcome of any asthma diagnosis, the sample size of 214 allows for detection of a 22% increase in the proportion with the outcome (relative risk 1.63) with 90% power ( $\beta = 0.10$ ) at a significance level of 5% ( $\alpha = 0.05$ ), assuming a baseline prevalence of 35% in the placebo group (as was found in the 6-8 year follow-up for the whole cohort).

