### Analysis approach

Analyses will be performed using an intention-to-treat approach with participants analysed according to the initial treatment group to which their mother was allocated. The denominator for the outcome of death (any cause after randomisation) will be the total number of fetuses alive at randomisation in the NZ cohort (n=352). All other study outcomes will use the total number of participants who gave consent (n=214).

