### Clustering

As 20% of the ACTORDS cohort were multiple pregnancies, clustering will be accounted for in this analysis using generalised linear mixed-effects regression models with inclusion of the unique maternal identifier as a random effect to account for the nonindependence of children from multiple pregnancies.

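### The 90% power in SAP section 8 assumes 214 independent children, although section 10 plans a clustered analysis because siblings are not independent; the loss is modest and its size depends on figures the SAP does not give

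*SAP*

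**What the plan says.** Section 8 (Power calculation) states that "the sample size of 214 allows for detection of a 22% increase in the proportion with the outcome (relative risk 1.63) with 90% power", at a 5% significance level and "assuming a baseline prevalence of 35% in the placebo group". It explains that the sample size is limited to the New Zealand participants who could be located. It mentions no siblings, design effect or intraclass correlation.

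Section 10 gives three further facts:

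- Under Clustering: "As 20% of the ACTORDS cohort were multiple pregnancies, clustering will be accounted for in this analysis". The method is a mixed-effects model with the mother's identifier as a random effect, because children of the same pregnancy are not independent.
- Under Analysis approach, children are analysed in the group to which their mother was allocated.
- The same paragraph sets the denominator for everything except death: "All other study outcomes will use the total number of participants who gave consent (n=214"). The denominator for death is the 352 fetuses alive at randomisation in the New Zealand cohort.

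**The concern.** Sections 8 and 10 describe different analyses. The power figure fits a comparison of 214 unrelated children. The planned analysis allows for siblings.

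Treatment was allocated to the mother, so twins are always in the same arm. A positive correlation between them then inflates the variance of the treatment comparison. The direction of the error therefore follows from the SAP's own statements, without any outside figure.

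What is at stake is how the study is described. A reader of the results would take it that a 22-point difference had a 90% chance of detection, when the planned analysis would probably have somewhat less. The estimates, confidence intervals and type I error are not at stake, because the analysis already models the clustering.

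**Working it through.** **Inputs from the SAP.** N = 214, control rate 35%, relative risk 1.63 and alpha 5% (section 8); multiples 20% (section 10, Clustering). The treated rate is 35% + 22 points = 57%, and 0.57/0.35 = 1.63, so the 22% is an absolute difference.

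**Assumptions, not in the SAP.** Two-sided test; 107 per arm (a 95:119 split gives 90.0%, so this matters little); twins only; ICC from 0.1 to 0.7, with 1.0 as the extreme.

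**Step 1: reproduce the 90%.** With mean rate 0.46 and a pooled-variance test,

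power = Φ{[0.22·√n − 1.96·√(2·0.46·0.54)] / √(0.35·0.65 + 0.57·0.43)}

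At n = 107: (0.22·10.344 − 1.96·0.7048)/0.6875 = 1.301, so power is **90.3%**. The arcsine method also gives 90.3%. An unpooled test gives 91.2%, a continuity correction 87.7% and Fisher's exact test 87.1%. The stated figure is thus the independence figure, with almost nothing to spare.

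**Step 2: how much clustering that margin can absorb.** Solving the formula for 90% gives n = 105.8 per arm, so the largest design effect (DE) compatible with 90% is 107/105.8 = 1.012.

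**Step 3: the design effect.** DE = 1 + q·ICC, where q is the share of analysed children whose co-twin is also analysed.

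- If 20% of pregnancies are twin, 100 pregnancies yield 80 + 40 = 120 children, so q = 40/120 = 0.333.
- If 20% of children are multiples, q = 0.20.

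Power falls below 90% once ICC exceeds 0.012/0.333 = 0.035 on the first reading, or 0.012/0.20 = 0.06 on the second.

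**Step 4: power with n = 107/DE.**

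| ICC | q = 0.333: DE | effective N | power | q = 0.20: DE | effective N | power |
|---|---|---|---|---|---|---|
| 0.1 | 1.033 | 207 | 89.4% | 1.020 | 210 | 89.8% |
| 0.3 | 1.100 | 195 | 87.4% | 1.060 | 202 | 88.6% |
| 0.5 | 1.167 | 183 | 85.4% | 1.100 | 195 | 87.4% |
| 0.7 | 1.233 | 174 | 83.4% | 1.140 | 188 | 86.2% |
| 1.0 | 1.333 | 160 | 80.4% | 1.200 | 178 | 84.4% |

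**Step 5: detectable difference at 90% power.** Under independence it is 21.9 points (RR 1.62). At q = 0.333 and ICC 0.5 it is 23.6 points (RR 1.67).

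**Step 6: incomplete pairs.** Consenters are 214/352 = 61% of fetuses alive at randomisation. If consent were independent between twins (an assumption; in practice it is probably correlated), q would fall from 0.333 to about 0.333·0.61 = 0.20. The first reading would then give the right-hand columns, about 87-90% for ICC 0.1 to 0.5.

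**The case against.** **The loss cannot be fixed at one value.** The SAP gives no ICC. Its 20% describes the whole ACTORDS cohort rather than the 214 New Zealand consenters, and it may mean pregnancies or children. Incomplete pairs would reduce the loss. All of this stands. A reader might infer a narrow true power, such as 84-88%, but the documents do not support one. At low ICC the loss is about one point or less.

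**The figure drives nothing.** The sample was fixed by who could be found and who consented, and the analysis already handles clustering. This also stands, and it limits the consequence. It does not make the stated figure right for the planned analysis.

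**A reader might go further and infer that a null result could not support the no-harm hypothesis.** The hypothesis is benefit "without long-term adverse impacts on health and social outcomes in offspring (F1"), and the SAP sets no margin. But that is a separate matter from clustering and would apply equally at 90% power. The SAP nowhere says that non-significance will be read as absence of harm, its Aim is neutral, and section 12 commits to relative risks with 95% confidence intervals. With 35% in both arms, SE(log RR) = √(2·0.65/(0.35·107)) = 0.186 and the interval is about 0.69 to 1.44; at DE 1.2 it is about 0.67 to 1.49. Such a result would exclude RR 1.63 but leave smaller increases open. The most that can be said is that non-significance alone does not show absence of harm.

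**The 22% increase could be misread as relative.** Taken as RR 1.22, power would be only 21%. But the same sentence gives RR 1.63 and the 35% baseline, so this is a matter of wording.

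**Conclusion.** The point holds in limited form. The 90% is the power for 214 independent children, and the SAP itself says that they are not independent. For any positive within-mother correlation the planned clustered analysis has less power than that calculation gives. Under the pooled formula it drops below 90% at an ICC of about 0.035 to 0.06.

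For an assumed ICC of 0.1 to 0.7, power is about 83-89% if one third of the children are in complete twin pairs and about 86-90% if one fifth are, with a floor near 80% at ICC 1. These ranges assume twins only, near-equal arms and a two-sided pooled test. They do not model the gestational-age adjustment or simulate the planned log-link mixed model. The loss is modest and affects the description of the study, not the validity of its analysis.

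**What to change.** Count the sibling sets among the 214, which needs neither outcome data nor treatment allocation. Then restate section 8 with a design effect based on that count and an explicit ICC range. Pending the count, the wording could be:

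> Allowing for siblings, power is about 83-90% for a difference of 22 percentage points (35% v 57%, RR 1.63), for an assumed within-mother ICC of 0.1 to 0.7. At ICC 0.5 with one third of children in twin pairs, 90% power needs about 23.6 percentage points (RR 1.67).

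Also write percentage points for the 22%, and say whether the 20% in section 10 means pregnancies or children.

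Optionally, and as a separate matter, add one sentence saying that a non-significant primary result does not by itself show absence of harm and will be interpreted through its 95% confidence interval.

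The cost is a few lines of SAP text and a slightly less favourable power statement. No analysis, outcome or sample size changes.

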## 9. Analysis based on Self-reported Outcomes

An aim of the ANCHOR research program was to compare outcomes based on expert clinical synthesis of administrative and self-reported data and those based on questionnaire responses completed by each participant. We have found that, while there are differences in the outcomes between these two data sources in 50-year-olds, overall differences between randomised groups remained the same regardless of the data source. Therefore, the synthesis of administrative and self-reported data will be used in this analysis.

## 10. General issues for statistical analysis

[Analysis software](#)

All analyses will be performed using R^8.

### Analysis approach

Analyses will be performed using an intention-to-treat approach with participants analysed according to the initial treatment group to which their mother was allocated. The denominator for the outcome of death (any cause after randomisation) will be the total number of fetuses alive at randomisation in the NZ cohort (n=352). All other study outcomes will use the total number of participants who gave consent (n=214).

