### Approach for withdrawals, missing data and outliers

Data up to the point of withdrawal will be used for those participants who have withdrawn from the study unless they have withdrawn their consent for use of their data. No imputation will be performed for missing data. We do not plan to exclude outliers from the analysis.

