| Primary outcome                                                                                                                                                                                                                                                                                                                                                      |                                        |                                                                                                                                                                                                                                                                                                                                                                                                             |                                                                                                                    |                                                                                                                                                                                                                     |
| Any asthma diagnosis
Defined as the presence of either of: 
 
Self-report of a doctor's diagnosis of asthma.
 
Hospital admissions with diagnostic codes for asthma at any age.
 
Dispensing of pharmaceuticals for asthma at any age at least one repeat prescription more than 1 day apart.
 
 | Self-report questionnaire              | B22. Have you ever been told by a doctor that you have asthma?                                                                                                                                                                                                                                                                                                                                              | If answers no to question about asthma but has evidence from only one other data source, then will be adjudicated. |                                                                                                                                                                                                                     |

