| 
(composite categorised as 0, 1 or >1 risk factors) – any of:
 
 
• high blood pressure
 
• dyslipidaemia
 
• diabetes mellitus (see following outcome)
 
• obesity/overweight
 
 
Defined as the presence of either of:
 
 
1. Self-report of a risk factor listed above.
 
2. Hospital admissions with diagnostic codes for a risk factor listed above.
 
3. Testsafe lab results of dyslipidaemia
 
4. Dispensing of a listed pharmaceutical for treatment of dyslipidaemia or hypertension
 
 |                                        | 
B3. Have you ever been told by a doctor that you have high blood cholesterol levels?
 
B18. Have you ever been told by a doctor that you have pre-diabetes or diabetes? (not including gestational diabetes)
 
BMI >25 as calculated using:
What is your current weight? (Q.F2)
What is your current height (Q.F3)
 |                                           |                      |
|                                                                                                                                                                                                                                                                                                                                                                                                                                                                                                                                                                                                                                                                                     | NMDS admissions data                   | 
Admissions with the following ICD-10AM codes:
 
Hypertension:
Essential hypertension; I110, I119
hypertensive heart disease; I120,
                                                                                                                                                                                  |                                           |                      |

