| General health outcomes: self-reported general health (reported health fair or poor)                                                                                                                                                                    | Self-report questionnaire              | E1. In general, would you say your health is ...                                                                                                                                                                                                                                                                                                                                                                                                                              |                                           |                                                                                                                                                                                                                                                                                                                                                                                                                                                                                                                                                 |

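### A fixed denominator of 214 for every outcome except death cannot be combined with the no-imputation rule for outcomes that only the questionnaire measures

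*SAP*

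**What the plan says.** Four parts of the SAP bear on this.

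- **Denominators (section 10, Analysis approach).** The denominator for death "will be the total number of fetuses alive at randomisation in the NZ cohort (n=352"). The next sentence reads: "All other study outcomes will use the total number of participants who gave consent (n=214"). No outcome is excepted for missing data.
- **Non-completers (section 5, repeated in Appendix 15.2).** Administrative data are censored at the questionnaire date "for participants who completed the questionnaire and at the date of consent for those who did not". The plan therefore allows for consenters without a questionnaire but does not say how many there are.
- **Missing data (section 10, Approach for withdrawals, missing data and outliers).** "No imputation will be performed for missing data".
- **Sources (Appendix 15.2).** General health rests on one item, "E1. In general, would you say your health is". Functional difficulties and oral health also have only self-report sources, as do unemployment, alcohol, recreational drugs, smoking in pack years, and vaping. Height and weight, and so BMI, come only from questionnaire items such as "What is your current weight? (Q.F2").

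The second addendum added the six functional-difficulty components and BMI, height and weight as tertiary outcomes. All nine depend on the questionnaire, and the denominator sentence was left as it was.

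**The concern.** For an outcome measured only by questionnaire, a consenter who returned none has no value. The analyst then has two options. Keeping the person in a denominator of 214 means scoring them as no event, or as no disability. That fills in a missing value and breaks the no-imputation rule. Leaving the person out breaks the denominator rule. The plan does not say which rule gives way.

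What is at stake is the reported proportions for these outcomes and, if completion differs between arms, their relative risks. The study hypothesis is that repeat corticosteroids have no long-term adverse effects. Undercounting adverse outcomes lowers the risks in both arms and shrinks any absolute difference, which favours a finding of no difference.

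**Working it through.** **1. The plan's own figure.** Section 8 gives 90% power with 214 participants for asthma at 35% v 57% (35% plus 22 points; 0.57/0.35 = 1.63). Assume 107 per arm (arm sizes are not given), a two-sided 5% test, pooled variance and no clustering:

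- mean risk = 0.46; null SE = √(2 × 0.46 × 0.54/107) = 0.0681
- alternative SE = √((0.35 × 0.65 + 0.57 × 0.43)/107) = 0.0665
- z = (0.22 − 1.96 × 0.0681)/0.0665 = 1.30, so power = 90.3%

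The figure reproduces. It concerns asthma, which also has admission and dispensing sources, so it does not test the present point.

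**2. Reach.** Questionnaire-only outcomes are 3 of 13 secondary outcomes, 5 of 8 stand-alone tertiary outcomes, the 6 functional-difficulty components, and BMI, height and weight.

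**3. Binary outcome, literal rule, equal non-response.** Let p be the true risk and q the non-response proportion, with response unrelated to the outcome. Then

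reported risk = p × (1 − q), and RR = p₁(1 − q) / [p₀(1 − q)] = p₁/p₀.

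With p = 20% and q = 10%: 0.20 × 0.90 = 18%. The RR does not change, but the risk difference does. The table borrows 35% v 57% for a hypothetical questionnaire-only outcome. The values of q are assumptions.

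| q | Reported risks | Risk difference (points) | Power, 214 kept | Power, responders only |
|---|---|---|---|---|
| 0 | 35.0% v 57.0% | 22.0 | 90.3% | 90.3% |
| 10% | 31.5% v 51.3% | 19.8 | 84.2% | 87.1% |
| 20% | 28.0% v 45.6% | 17.6 | 76.5% | 82.9% |
| 30% | 24.5% v 39.9% | 15.4 | 67.6% | 77.6% |

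**4. Binary outcome, literal rule, unequal non-response.** Reported RR = true RR × (1 − q_repeat)/(1 − q_placebo). With a true RR of 1.00:

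- completion 85% repeat, 95% placebo: 0.85/0.95 = 0.89
- completion 95% repeat, 85% placebo: 0.95/0.85 = 1.12

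**5. Continuous outcomes.** Height, weight and BMI have no default value for a non-responder, so 214 cannot be reached. For pack years, entering zero would itself be an imputation.

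**6. Number of cardiovascular risk factors.** This outcome has several sources. Hypertension and diabetes can come from admissions, dyslipidaemia from laboratory results, and hypertension or dyslipidaemia from dispensing. Overweight or obesity comes from BMI or from an admission code for obesity. A non-completer can therefore score 1 or more. Category 0, however, requires knowing that the person is not overweight, and without BMI the listed sources do not show that.

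**The case against.** The strongest reply is that 214 names the analysis population and is not a literal divisor. The sentence stands in the intention-to-treat paragraph. The no-imputation rule would make the regression models drop a missing outcome. The enriched analysis in section 13 speaks of outcomes missing at 20 years and corrects denominators to participants with data. On this reading, non-responders simply stay missing.

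Part of this stands. No section says that non-responders are event-free, so a reader who takes that as the stated plan goes beyond the document. It is only what follows if the denominator rule is applied as written. But the reply does not remove the conflict. The preceding sentence sets the denominator for death, and this one sets it for all other outcomes. The corrected denominators in section 13 apply only to an exploratory analysis. If the authors do intend missing values to drop out, the sentence in section 10 is wrong as written and needs the same edit.

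The reply is also right that the size is unknown and that equal completion leaves the RR, the reported measure for binary outcomes, unchanged.

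Two stronger inferences should be resisted:

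- **Non-completers can only enter as having no cardiovascular risk factors.** The other listed sources show otherwise (step 6).
- **The primary outcome is ascertained wrongly for non-completers.** The appendix says: "If answers no to question about asthma but has evidence from only one other data source, then will be adjudicated". A reader might object that a non-completer with one source becomes a case without review. But one qualifying source meets the stated definition, and adjudication is triggered by a contradictory answer, which a non-completer has not given. Wider adjudication would be a preference, not the correction of an error.

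**Conclusion.** The point holds as a conflict between two stated rules. For questionnaire-only outcomes, the denominator of 214 and the ban on imputation cannot both be followed once any consenter lacks a questionnaire. Three secondary outcomes and a larger set of tertiary ones are affected. The primary outcome is not.

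If the denominator rule is followed literally, each reported risk on a binary outcome is multiplied by the arm's completion proportion. The 18% for a true 20%, and the RR of 0.89 or 1.12 for a true 1.00, are illustrations. They rest on assumed completion rates and on response being unrelated to the outcome. The document does not show that completion differed by arm, so no actual bias in a relative risk can be claimed from it.

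**What to change.** Replace the sentence in section 10 with outcome-specific denominators, for example:

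> For outcomes whose only source is the questionnaire, the denominator is the consenting participants who answered the relevant item(s). For outcomes that linked administrative data can ascertain, the denominator is all 214 consenting participants. The number analysed is shown for each outcome and arm.

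Also:

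- Report questionnaire non-completion by arm, so that readers can judge whether differential response is plausible.
- For the number of cardiovascular risk factors, do not place a participant in category 0 when BMI is missing and no other source establishes overweight or obesity.

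The cost is a short addendum, an n on each row of the results tables, and a re-run of any outcome for which 214 was used literally. The downside is that some stated n fall below 214.
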